## Methods: participants, interventions and outcomes

### Study setting {9}

This is a multicenter study involving two facilities within the Cleveland Clinic Foundation hospital system. The Cleveland Clinic Center for Abdominal Core Health, a center within the Digestive Disease and Surgery Institute (DDSI), at Cleveland Clinic Main Campus in Cleveland, Ohio, is the hosting department for the study. The second facility involved in the study is Cleveland Clinic Fairview Hospital in Cleveland, Ohio.

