### Sample size {14}

Assuming a 20% rate of loss to follow-up, enrollment of 240 participants with 120 participants in each arm will provide at least 80% power for showing superiority of anterior gastropexy to no anterior gastropexy for the primary endpoint of decreased recurrence rates by 15% at the 1-year postoperative visit using a two-sided chi-square test and an alpha level of 5%. For the purpose of calculating the power of this study, the proportion of recurrences in the control group (no anterior gastropexy) is estimated to be 0.24. This is based on the reported recurrence rates for paraesophageal hernia repair without gastropexy, ranging from 7 to 66% [3, 16, 21–24], with the majority falling between 13 and 42% [3, 16, 23, 24] at various time points after surgery.

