#### Statistical methods

##### Statistical methods for primary and secondary outcomes {20a}

All analyses will be performed using the intent-to-treat population and will be done under the normality assumption, if appropriate. Patient characteristics will be summarized overall and by randomized group, and differences will be described as standardized effects. All tests will be considered significant at 5% level. Outliers for each endpoint will be assessed with a graphical method, such as the box plot. All primary and secondary endpoints will be initially evaluated using all observations and then evaluated with a sensitivity analysis without including points identified as outliers. All statistical analyses will be performed with SAS software (version 9.4; Cary, NA) or R software (version 4.0.0, 2020-04-24; Vienna, Austria).

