##### Primary outcome

The primary endpoint of this study is radiographic recurrence rates at 1 year following either anterior gastropexy (intervention) or no anterior gastropexy (control) during paraesophageal hernia repair. Differences between the two groups will be tested and described using a binomial regression model with identity link and robust variance estimation. Pre-specified covariates will include fundoplication vs. no fundoplication, Type II/III vs. Type IV PEH, body mass index (BMI), sex, and surgeon, with the surgeons modeled as cluster effect. Results will be presented as relative risk and absolute risk differences with a 95% confidence interval. In cases where the model fails to run due to convergence issues, a Poisson GEE model with robust variance estimates, a log Poisson regression model, or a linear regression GEE model with exchangeable correlation and robust standard errors will be used to estimate the risk difference.

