#### Oversight and monitoring

##### Composition of the coordinating center and trial steering committee {5d}

Study coordination and trial steering will be carried out by the Cleveland Clinic Center for Abdominal Core Health research team within the DDSI department at Cleveland Clinic Foundation, Cleveland, Ohio. The research team consists of several faculty surgeons who serve as either the PI or Co-I’s, one clinical research nurse and several research fellows, residents, and medical students. The entire research team meets weekly to evaluate study progression, adverse events, and any updates to study procedures and requirements. The research team performs the functions of a steering committee, endpoint adjudication committee, data management team, and oversight team. Day-to-day trial organization and data management are the responsibility of the dedicated research residents, fellows, and clinical nurse on the research team. The PI and Co-I’s will oversee the progression of the study, ensure adherence to protocol, and provide guidance with publication.

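### The primary test's robust variance, on its most natural reading, is clustered on an unstated and probably small number of surgeons; uncorrected this breaks the 5% level, corrected it loses the planned power

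*Protocol article*

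**What the plan says.** All places are in the protocol article.

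- *Statistical methods {20a}, Primary outcome*: the arms are compared by binomial regression with identity link and robust variance. The covariates are fundoplication, hernia type, "body mass index (BMI), sex, and surgeon, with the surgeons modeled as cluster effect". If the model does not converge there are three alternatives: a Poisson GEE with robust variance, a log Poisson regression, or "a linear regression GEE model with exchangeable correlation and robust standard errors will be used to estimate the risk difference".
- *Statistical methods {20a}*: "All tests will be considered significant at 5% level".
- *Study setting {9}*: "This is a multicenter study involving two facilities within the Cleveland Clinic Foundation hospital system".
- *Composition of the coordinating center {5d}*: "The research team consists of several faculty surgeons who serve as either the PI or" co-investigator. *Implementation {16c}* identifies the participating surgeons with these same roles. *Recruitment {15}* leaves open adding further surgeons. No section gives a count.
- *Intervention description {11a}* and *Sequence generation {16a}*: each patient is randomised 1:1 during the operation, with no restriction, so not by surgeon and not stratified by surgeon.
- *Sample size {14}*: 240 patients "will provide at least 80% power for showing superiority" on a plain patient-level two-sided chi-square test at 5%.

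**The concern.** A sandwich variance clustered on surgeon estimates variability from G surgeon-level totals, not from 240 patients. When G is small it is biased downward and unstable, and a normal reference ignores that instability. The test then rejects too often and the interval is too short.

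The design does not call for this clustering. Patients are randomised within each surgeon's practice, so a surgeon's general recurrence level affects both arms alike. Surgeon is a prognostic factor to adjust for, not the unit of randomisation.

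This is the trial's only primary test. The article's abstract expects a positive result to make gastropexy routine and a negative one to end its use, so the error rate of this test matters directly.

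**Working it through.** **1. Inputs.** From *Sample size {14}*: "the proportion of recurrences in the control group (no anterior gastropexy) is estimated to be 0.24", a 15-point reduction (so 0.09 with gastropexy), 20% loss, 120 per arm, two-sided 5%. Evaluable: 0.8 × 120 = 96 per arm. Assumed, because not stated: the number of surgeons G (3 to 10, shown from 2 to 20) and a modest between-surgeon spread.

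**2. The plan's own figure.** With mean proportion 0.165:

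n = [1.96·√(2·0.165·0.835) + 0.842·√(0.24·0.76 + 0.09·0.91)]² / 0.15² = (1.029 + 0.433)² / 0.0225 ≈ 95 per arm.

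95/0.8 = 118.75, so 119 per arm or 238 in total, against 240 stated. The sample size reproduces, for a patient-level test.

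**3. Approximation for the clustered test.** With equal caseloads the arm effect is roughly the mean of G within-surgeon differences d_g. The uncorrected sandwich is Σ(d_g − d̄)²/G², whereas the unbiased variance is Σ(d_g − d̄)²/[G(G−1)]. The z statistic therefore behaves like t(G−1) multiplied by √(G/(G−1)), and

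type I error = P(|t(G−1)| > 1.96·√((G−1)/G)).

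For G = 3 the cut-off is 1.96·√(2/3) = 1.60, and P(|t(2)| > 1.60) = 1 − 1.60/√(2 + 1.60²) = 0.25.

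**4. Simulation under no effect.** 240 patients, 24% recurrence in both arms, intra-surgeon correlation 0 or 0.05, equal to unequal caseloads, without and with covariates, 4,000 runs per setting:

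| Surgeons | Formula | Simulated type I error |
|---|---|---|
| 2 | 40% | 39–43% |
| 3 | 25% | 25–29% |
| 4 | 19% | 19–22% |
| 5 | 15% | 15–19% |
| 6 | 13% | 13–17% |
| 8 | 11% | 11–15% |
| 10 | 10% | 8–13% |
| 15 | 8% | 8–12% |
| 20 | 7% | 7–11% |

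Actual GEE fits (binomial identity and linear exchangeable, 700 runs each) gave 22–24% at 3 surgeons, 14–17% at 5, 10–12% at 8 and 8–9% at 10. Intra-surgeon correlation hardly mattered, because treatment varies within surgeon. Results were about the same with 192 patients as with 240.

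**5. Interval width.** At 24% in both arms the patient-level standard error is √(2·0.24·0.76/120) = 0.0551, a half-width of 1.96 × 0.0551 = 10.8 points. The clustered standard error was typically 0.63–0.68 of the patient-level one at 3 surgeons and 0.85–0.92 at 10. That gives half-widths of about 6.8–7.3 and 9.2–9.9 points.

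**6. Keeping the clustering but correcting it.** G/(G−1) scaling with t(G−1) gave type I error of 4.2–5.6% with equal caseloads and 5.2–8.3% with unequal caseloads and covariates. The Mancl-DeRouen variance with t(G−1) gave 2.1–4.3%. The cost is power. With 96 per arm the standard error is √((0.24·0.76 + 0.09·0.91)/96) = 0.0525, so the noncentrality is 0.15/0.0525 = 2.86. The critical value is 4.30, 2.57 and 2.26 at 3, 6 and 10 surgeons. The noncentral t then gives power of 36%, 63% and 72%. Simulation gave about 40–73% across 3 to 10 surgeons.

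**7. Surgeon indicators with patient-level robust errors.** Type I error 4.5–6% and power 76–83% over the same range.

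**The case against.** Four points on the other side carry weight.

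- **The wording is not explicit.** Surgeon is listed as a covariate and as a cluster in the same sentence, and the level of the robust variance is never stated. The secondary outcomes use surgeon random effects. If the primary analysis means a fixed or random surgeon effect with patient-level errors, type I error is close to 5–6% and there is no material problem. Against this, the secondary-outcome section names random effects outright while the primary section does not. Exchangeable correlation also needs a cluster, and surgeon is the only one named. The clustered sandwich remains the more natural reading, and the sentence needs correcting if something else was meant.
- **A correction may sit in an unseen analysis plan.** That is possible, and its absence from an article is not a fault. But a correction does not restore the stated power, so the choice of cluster still has to be settled.
- **Not every fallback clusters.** The log Poisson alternative names no clustering.
- **Clustering can be deliberate**, if the gastropexy effect is thought to vary by surgeon and inference to surgeons in general is wanted. The article states no such aim.

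A reader might infer that this trial's primary test has a false-positive rate of 10–29% as a fact. The documents do not support that: the figure depends on a surgeon count they do not give and on the uncorrected normal-reference version. Nor is it right that a t reference cannot help. With scaling it largely repairs the error rate, at the expense of power.

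**Conclusion.** The concern holds in conditional form. On its most natural reading, the primary variance is clustered on surgeon in a trial that randomises individual patients. If about 3 to 10 surgeons operate, the uncorrected test has a type I error of roughly 10–29% instead of 5%, still about 9–10% at 15 surgeons, and its interval is too narrow. A corrected version holds about 5–7% but has about 40–73% power instead of 80%. So with few surgeons the clustering costs either the stated error rate or the stated power. This rests on the assumed surgeon count, on the clustered reading of the primary-outcome section, and on the planning rates of 24% and 9%. The sample size calculation itself is sound for the patient-level test it describes.

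**What to change.** In the primary identity-link model and the GEE fallbacks, enter surgeon as fixed indicators, pooling surgeons with few patients. Compute robust standard errors at patient level and state that level. Replace the closing clause of "body mass index (BMI), sex, and surgeon, with the surgeons modeled as cluster effect" accordingly, and report the number of operating surgeons. Settle this before outcomes are analysed.

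The cost is a wording change, with no extra patients or data. The model gains a few parameters, which may trigger the convergence fallback more often. The interval will be wider than the falsely narrow one.

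If surgeon clustering is kept on purpose, name a few-cluster correction with a t(G−1) reference and restate the power for the actual number of surgeons.

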##### Secondary outcomes

Secondary outcomes include patient-reported symptoms of GERD, dysphagia, odynophagia, gas bloat, regurgitation, chest pain, abdominal pain, nausea, vomiting, postprandial pain, cardiovascular, and pulmonary complaints along with patient satisfaction from GERD-HRQL and the numeric rating scale measured at baseline, 30 days postoperatively, and 1 year postoperatively. Generalized linear mixed effect models will be used to compare categorical outcomes, and linear mixed effect models will be used to compare numeric continuous score outcomes. In these models, groups will be analyzed using fixed effect parameters and surgeons will be analyzed using random effect parameters.

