### Objectives {7}

The primary objective of this trial is to investigate the rates of radiographic PEH recurrence at 1 year in patients receiving anterior gastropexy compared to those receiving no anterior gastropexy during minimally invasive PEHR. The cumulative recurrence rates for laparoscopic PEHR with anterior gastropexy ranges from 0 to 25% [12, 15–20], compared to the recurrence rates without anterior gastropexy ranging from 7 to 66% [3, 16, 21–24]. This data is limited by variable lengths of follow-up and definitions of recurrences. We hypothesize that anterior gastropexy will result in a 15% reduction in PEH recurrence after minimally invasive repair compared to no gastropexy. Based on previously published data and our group consensus, we feel that a 15% reduction is a conservative but clinically important difference that supports the routine use of anterior gastropexy during PEHR.

Secondary objectives include the rates of symptomatic gastroesophageal reflux disease (GERD), dysphagia, odynophagia, gas bloat, regurgitation, chest pain, abdominal pain, nausea, vomiting, postprandial pain, cardiovascular, and pulmonary symptoms as well as patient satisfaction in the immediate postoperative and 1-year follow-up periods between the two groups.

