**ASSESSMENTS:**				
**PEH recurrence**				**X**
**GERD**	**X**		**X**	**X**
**Dysphagia**	**X**		**X**	**X**
**Odynophagia**	**X**		**X**	**X**
**Gas bloat**	**X**		**X**	**X**
**Regurgitation**	**X**		**X**	**X**
**Chest pain**	**X**		**X**	**X**
**Abdominal pain**	**X**		**X**	**X**
**Nausea**	**X**		**X**	**X**
**Vomiting**	**X**		**X**	**X**
**Postprandial pain**	**X**		**X**	**X**
**Cardiovascular symptoms**	**X**		**X**	**X**
**Pulmonary symptoms**	**X**		**X**	**X**
**Patient satisfaction**			**X**	**X**
**Demographic data**	**X**			
**Operative details**		**X**		
**Wound morbidity**			**X**	
**Medical morbidity**			**X**	
**Length of stay**			**X**	
**Readmission**			**X**	**X**

*PEH* paraesophageal hernia, *GERD* gastroesophageal reflux disease

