### Methods in analysis to handle protocol non-adherence and any statistical methods to handle missing data {20c}

Missing data over time is anticipated to reflect a pattern of “missing at random.” Data collection at the time of the initial surgical consultation (enrolment period) and during the operation (randomization period) will be negligible, as we will ensure capture of all necessary measurements during these time points. If necessary, multiple imputation will be used to impute missing baseline data. Provided that the “missing at random” assumption holds true, multiple imputation of follow-up measurements will not be performed. Since this study involves surgical intervention at the time of randomization, non-adherence to the intervention is not expected to occur.

For missing data during the follow-up period, mixed effect models will be used, which by virtue of their maximum likelihood approach will provide reliable estimates when missing data are “missing at random.” This assumption will be graphically evaluated, and if necessary, sensitivity analyses will be performed to assess the robustness of our findings. This approach will be used for all secondary endpoints.

As for the primary endpoint, obtaining 1-year radiographic assessments will be the most challenging aspect of this study. Several mechanisms are in place to account for missing radiologic data. First, a 20% loss to follow-up rate is expected and was incorporated into the sample size calculation during study development. Second, “intent-to-treat” analysis will be performed, and the “last value carried forward” method will be applied to missing observations. In this method, patients who are lost to follow-up will be considered as “no recurrence,” and the total patient population of 240 will remain as the denominator. Lastly, tipping point analysis will be performed as a sensitivity analysis to examine how missing 1-year radiographic follow-up data affects the validity of our findings.

If non-random missing data patterns are observed, alternate sensitivity analyses, such as pattern mixture models, will be considered.

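### The model terms named for the secondary symptom outcomes (group and surgeon) do not fit scores taken three times per patient, the per-period objectives, or the missing-at-random claim

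*Protocol article*

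**What the plan says.** The Secondary outcomes part of the statistical methods lists twelve symptoms plus satisfaction, "measured at baseline, 30 days postoperatively, and 1 year postoperatively". It says that "linear mixed effect models will be used to compare numeric continuous score outcomes", with generalized linear mixed models for categorical outcomes, and then gives the terms: "In these models, groups will be analyzed using fixed effect parameters and surgeons will be analyzed using random effect parameters". The article names no other term for these outcomes.

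Three other places bear on this:

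- Objectives {7} sets the comparison of symptoms and "patient satisfaction in the immediate postoperative and 1-year follow-up periods between the two groups". Baseline is not one of those periods.
- Section {20c}, on missing data, assigns missing follow-up for all secondary endpoints to mixed models, "which by virtue of their maximum likelihood approach will provide reliable estimates when missing data are" missing at random. Under that assumption it rules out multiple imputation of follow-up measurements.
- Table 1 schedules the symptoms at all three times, but satisfaction only at 30 days and 1 year.

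**The concern.** Each patient contributes up to three correlated scores, the first taken before randomization. A surgeon random effect links patients of the same surgeon. It does not link the scores of one patient, and it does not separate visits. The named terms therefore leave open what the group coefficient estimates, whether its standard error is right, and whether a patient's earlier scores inform a missing later one.

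This matters for the trial's own question. The Background gives short-term pain at the fixation site as a reason why surgeons avoid gastropexy, set against an unclear long-term benefit. Early harm and later benefit must be seen separately, and one coefficient across visits could offset them. Every test is read at the 5% level (Statistical methods {20a}), over twelve symptoms and satisfaction, so an understated standard error would produce extra false positives.

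**Working it through.** The document gives no figure for the secondary outcomes, so there is none to reproduce. Two ways of applying the named terms are worked through.

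**Inputs from the protocol.** Three measurement times; 120 patients per arm; 20% loss to follow-up, leaving 0.80 × 120 = 96 per arm; 5% level.

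**Assumptions, not in the protocol.** Within-patient correlation ρ of 0.3, 0.5 and 0.7, equal between visits; score SD of 1; a shift of δ SD from baseline to both follow-ups; an illustrative effect of 0.40 SD.

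**Reading A: all three visits in one model with group and surgeon**

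*What is estimated.* The group coefficient is the average of the visit-specific differences, weighted by the scores available. The expected baseline difference is 0 by randomization.

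- Complete data, equal effect d at both follow-ups: (0 + d + d)/3 = 0.67d.
- Complete data, effect at 1 year only: d/3 = 0.33d.
- 20% missing at 1 year, with weights 1, 1 and 0.8 (total 2.8): equal effect 1.8/2.8 = 0.64d; 1-year-only effect 0.8/2.8 = 0.29d, so 0.40 SD is estimated as 0.11 SD.
- Effects of +0.4 SD at 30 days and −0.4 SD at 1 year, same missingness: (0.4 − 0.8 × 0.4)/2.8 = 0.03 SD.

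*Type I error.* With complete data, the true variance of a patient's mean of three scores is (1 + 2ρ)/3. A model without a patient term, but with visit, takes it to be 1/3. The ratio is V = 1 + 2ρ and the true two-sided error is 2[1 − Φ(1.96/√V)].

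Without a visit term, the unmodelled shift enters the residual variance. The visit means 0, −δ, −δ have variance (2/9)δ², so V = (1 + 2ρ)/(1 + (2/9)δ²).

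| Model | ρ = 0.3 | ρ = 0.5 | ρ = 0.7 |
|---|---|---|---|
| Visit modelled, or no shift: V | 1.60 | 2.00 | 2.40 |
| Type I error | 12.1% | 16.6% | 20.6% |
| No visit term, δ = 1: V | 1.31 | 1.64 | 1.96 |
| Type I error | 8.7% | 12.6% | 16.2% |
| No visit term, δ = 1.5: V | 1.07 | 1.33 | 1.60 |
| Type I error | 5.8% | 9.0% | 12.1% |

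Simulation with 96 per arm, six surgeons and surgeon variance 0.02 (both assumed), with 400 trials per setting, gave 9.8%, 14.3% and 20.0% with a visit term. Without one, at δ = 1, it gave 7.8%, 8.5% and 14.5%. The pattern is the same, with the noise expected from 400 runs.

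**Reading B: each follow-up visit modelled separately with group and surgeon**

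- Each patient appears once per model, so there is no dilution and no repeated-measures error. Simulation gave type I error of about 5 to 6% and recovered a 0.40 SD effect as 0.39 to 0.40 SD.
- The baseline is unused. With 96 per arm, the standard error of the 1-year difference is √(2/96) = 0.144 without baseline and √(2(1 − ρ²)/96) with it: 0.138, 0.125 and 0.103 at the three correlations. Power for 0.40 SD, Φ(0.40/SE − 1.96), is 79% without baseline against 83%, 89% and 97% with it.
- A patient without a 1-year score contributes nothing to the 1-year model. That is a complete-case analysis. Maximum likelihood protects against missingness that depends on earlier scores only if those scores are in the same likelihood and linked to the missing one. Here they are not.

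**The passages side by side.** Reading A answers neither of the two periods in Objectives {7}. It also lacks the patient-level link that {20c} presupposes. Reading B meets Objectives {7} but leaves {20c} without its basis. With only the named terms, no reading satisfies both.

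**The case against.** The strongest reply is that the article does not say these are the only terms, nor that the three visits are stacked in one model. It condenses a fuller protocol, and visit terms, covariance structure and baseline adjustment are often left to an analysis plan that is not shown. Objectives {7} suggests separate comparisons at each period. Section {20c} suggests a longitudinal model. Either would avoid the worst consequences.

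Much of this stands. A reader might infer that the plan does average in the baseline and does treat a patient's scores as independent. The text does not support that as a statement of fact; it is what follows if the named terms are applied to pooled visits. A reader might also take 12 to 21% as the error rate of the literal model. Those figures need visit in the model, or no change in scores after repair. Without a visit term the rate is lower, and near nominal in the mildest case above.

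What does not stand is that nothing needs fixing. The article does specify model terms here, and for the primary outcome it goes as far as link, covariates and clustering. The terms it gives for the secondary outcomes do not support the missing-data claim that it makes for the same models.

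**Conclusion.** The point holds as an inconsistency among the Secondary outcomes model, Objectives {7} and section {20c}. Under pooling, the effect is diluted to about 2/3 (equal at both follow-ups) or about 1/3 or less (1 year only). Type I error is then roughly 8 to 20%, falling to about 6% at the lowest correlation if scores shift by 1.5 SD and visit is omitted. Under separate models the tests are valid, at the cost of an unused baseline and an unsupported missing-at-random argument.

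The error rates and power figures rest on the assumed correlations, shift and effect; the dilution fractions do not depend on the correlation. Satisfaction differs, because Table 1 gives it no baseline although the statistical section lists it with outcomes measured at baseline. The primary endpoint has its own model and the sample size is unaffected.

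**What to change.** For each symptom score, state one model for the 30-day and 1-year scores together:

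- baseline score as a covariate;
- visit, group and group-by-visit as fixed effects;
- a patient random intercept or an unstructured within-patient covariance;
- surgeon kept as the planned random effect.

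Use the analogous generalized mixed model for categorical outcomes. Report the group difference separately at 30 days and at 1 year. For satisfaction, omit the baseline covariate and correct the sentence that lists it as measured at baseline. The argument in {20c} then has the patient-level link it needs, and the multiple imputation already provided there for missing baseline data can serve the covariate.

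The cost is a change of analysis wording, best made before the data are analysed. It needs no new patients, visits or measurements, since the scores are already scheduled in Table 1.
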